### Onboarding and monitoring

Participants will receive standardized onboarding and device training, including in-clinic instruction when feasible and structured digital training materials. Training will emphasize correct headset placement and session initiation. Adherence will be monitored using application-generated usage logs, including session date, time, and completion status, which are accessible to the research team. Participants may be contacted weekly during the preoperative period to assess tolerability, address technical issues, review adherence, and screen for emerging concerns.

Deviations from the intended treatment schedule (e.g., missed sessions, delayed or rescheduled surgery dates) will be documented to support interpretation of feasibility outcomes and planned sensitivity analyses.

Tolerability will be explicitly assessed during onboarding sessions. Participants who experience intolerable adverse effects at the protocol-specified 2 mA intensity during initial onboarding (e.g., severe scalp discomfort, headache not relieved by standard measures, or other adverse effects leading to participant request to discontinue) will be documented as onboarding-phase discontinuations.

### Concomitant care

All participants will continue to receive standard surgical and perioperative care without modification. Concurrent treatment for depression, including pharmacotherapy and/or psychotherapy, will be permitted. Changes in depression-related treatment during the intervention and follow-up period—including medication initiation, discontinuation, or dose adjustment, as well as psychotherapy initiation—will be recorded systematically to support contextualization of outcome trajectories and exploratory sensitivity analyses.

### Follow-up schedule and study procedures

Participants will complete baseline assessments before initiation of tDCS (Supplementary Table S1—SPIRIT Schedule Breakdown). Depressive symptoms will be assessed longitudinally through the preoperative period, including interim assessments prior to surgery. Postoperative assessments will be collected at prespecified intervals, including early postoperative timepoints (2 and 6 weeks) and longer-term follow-up at 3, 6, and 12 months. Postoperative measures will focus on pain intensity, opioid utilization, functional outcomes, and health-related quality of life.

Participants who do not proceed to surgery will continue to be followed for preoperative and intervention-related outcomes, including depressive symptom trajectories, feasibility, and acceptability measures (Figure 3). However, endpoints that are specific to the postoperative recovery period will not be collected for these participants.

### Safety monitoring and stopping considerations

Expected risks of tDCS are primarily mild and transient, including headache, scalp discomfort, and skin irritation. Safety monitoring will occur throughout the intervention via participant self-report, scheduled study team check-ins, and systematic documentation of adverse events. Participants will be able to contact the research team at any time via a dedicated contact number. Adverse events (AEs) and serious adverse events (SAEs) will be recorded, assessed for severity and relatedness, and managed according to pre-specified procedures; tDCS-specific AEs will be assessed via the tDCS Adverse Events Questionnaire preoperatively (Brunoni et al., 2011). In the event of unanticipated device-related SAEs or emerging safety concerns, study procedures may be paused or halted in coordination with institutional oversight and applicable regulatory requirements.

A predefined mental health escalation pathway will be implemented for participants with clinically significant worsening of depressive symptoms or emergent suicidality. This pathway will include prompt clinical assessment and referral to appropriate mental health services when indicated (Appendix A).

### Data collection and management

Study data will be collected using secure electronic data capture tools [e.g., REDCap, (2026).] for participant-reported outcomes and study questionnaires, supplemented by abstraction of relevant clinical variables from the electronic health record as needed. Device and application-generated usage logs will be used to capture adherence and session completion metrics. Data will be stored in institutionally approved secure systems with access restricted to authorized study personnel. Data handling will follow applicable institutional policies and HIPAA requirements (Health Information Privacy, 2026). In addition, baseline pain and anxiety symptoms will be assessed using the Pain Catastrophizing Scale (PCS) and Generalized Anxiety Disorder-7 (GAD-7), respectively, to better characterize the cohort and support exploratory adjustment in analyses.

### Outcomes

#### Primary outcomes: feasibility and acceptability

The primary outcomes of this study are the feasibility and acceptability of delivering a preoperative, home-based tDCS intervention using the Flow device in elective lumbar spine surgery patients with MDD. Feasibility will be evaluated across two complementary domains: treatment initiation and overall treatment exposure. Feasibility of initiation will be defined as the proportion of enrolled participants who complete at least 15 tDCS sessions within the first 21 days, corresponding to successful completion of the intensive initiation phase. Feasibility of exposure will be assessed as the proportion of participants achieving each pre-specified exposure tier prior to surgery, reflecting the ability to sustain treatment over a variable preoperative timeframe.

Acceptability will be evaluated through structured measures of treatment satisfaction, usability, and tolerability, complemented by qualitative participant feedback. Treatment satisfaction will be assessed preoperatively using a structured questionnaire incorporating 5-point Likert items adapted from prior home-based tDCS feasibility work, evaluating overall acceptability (“very acceptable” to “very unacceptable”), perceived benefit, and willingness to recommend the intervention. Usability will be assessed using the System Usability Scale (SUS), a validated 10-item instrument yielding a normalized 0–100 score, administered preoperatively (Brooke, 1996). A brief semi-structured exit interview will be conducted at the preoperative timepoint to capture qualitative themes related to tolerability, integration into daily routines, and perceived burden. Tolerability will additionally be assessed by the frequency and nature of adverse effects, including those that lead to treatment interruption or discontinuation. Reasons for treatment discontinuation will be systematically recorded and categorized. Together, these outcomes are intended to characterize whether preoperative home-based tDCS can be.

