**Figure 2 fig2:**
[figure not shown]
User wearing the flow neuroscience headset (Flow neuroscience patient sign-up, 2026). Source: Images were reproduced, with permission, from the parent company - Flow Neuroscience.

We hypothesize that most enrolled participants will be able to initiate treatment, defined as completion of the tDCS initiation phase within the first 3 weeks, and that a substantial proportion will achieve at least the minimum pre-specified treatment exposure before surgery. We further hypothesize that the intervention will be acceptable and well-tolerated, as reflected by high adherence, low rates of discontinuation due to adverse effects, and favorable participant-reported satisfaction.

A key exploratory clinical objective of the study is to assess preliminary changes in depressive symptom severity associated with preoperative home-based tDCS. The principal exploratory clinical outcome is change in depressive symptoms, measured using the self-reported Montgomery–Åsberg Depression Rating Scale (MADRS-S), consistent with prior home-based tDCS studies. We hypothesize that participants will demonstrate a reduction in depressive symptom severity from baseline to the preoperative assessment, with measurable improvement evident following completion of the intensive initiation phase.

Additional exploratory objectives include examining whether preoperative tDCS exposure is associated with changes in perioperative recovery-relevant outcomes. These exploratory outcomes include spine-related disability measured using the Oswestry Disability Index (ODI); back and leg pain intensity assessed via numeric rating scales; pain-related function measured using the PROMIS Pain Interference short form; and overall physical function measured using the PROMIS Physical Function short form. Opioid exposure will be assessed using standardized morphine milligram equivalent (MME) calculations, including baseline outpatient opioid use and postoperative opioid utilization across inpatient and outpatient settings.

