**Figure 3 fig3:**
[figure not shown]
CONSORT-style participant flow diagram. Participants are identified through spine surgery clinic schedules and screened for eligibility. Enrolled participants initiate home-based tDCS and are classified by pre-specified exposure tier based on the number of sessions completed. Following the intervention period, participants who proceed to elective lumbar spine surgery enter postoperative follow-up. Participants who do not proceed to surgery are followed for pre-operative and intervention-related outcomes only; postoperative recovery endpoints are not collected for this subgroup. All participants are included in the primary as-treated analysis by exposure tier achieved. Source: Images were reproduced, with permission, from the parent company - Flow Neuroscience.

The study is designed to prioritize feasibility and acceptability, with an exploratory assessment of changes in depressive symptom severity. Because the interval between surgical decision-making and operative intervention varies across patients, the intervention is delivered using a dose-to-time model with pre-specified exposure tiers based on the number of tDCS sessions completed before surgery.

As a pilot study, the design aims to (1) operationalize home-based neuromodulation within a perioperative spine surgery workflow, (2) quantify feasibility, acceptability, and safety, and (3) generate preliminary estimates of symptom change and variability to inform the design of future controlled trials. The protocol is reported in accordance with SPIRIT recommendations for interventional trial protocols (Supplementary Table S1).

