#### Feasibility criteria

Feasibility will be evaluated across recruitment, initiation/adherence, acceptability, retention, and safety domains. The study will be considered feasible if (1) ≥ 60% of initiated participants achieve the minimum preoperative exposure target (Tier A, ≥15 total sessions completed before surgery); (2) overall retention is ≥50% for the preoperative assessment and ≥40% for the 30-day postoperative follow-up; (3) acceptability is supported by a mean treatment satisfaction/usability score ≥4/5 and ≤20% discontinuation attributable to device-related adverse effects or burden; and (4) safety is supported by no device-related serious adverse events, ≤10% escalation for emergent psychiatric concerns, and an adverse event profile consistent with expected transient tDCS effects (e.g., mild headache or scalp discomfort). Feasibility outcomes will be summarized descriptively with 95% confidence intervals and used to refine recruitment workflows, dosing schedules, and monitoring procedures for a subsequent randomized trial.

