#### Analysis populations

The primary analytic population will include all enrolled participants who initiate the tDCS intervention. Participants will be analyzed on an as-treated basis, categorized according to the pre-specified exposure tier achieved before surgery. Sensitivity analyses may be performed using alternative adherence thresholds to assess the robustness of feasibility findings.

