#### Sample size justification

The sample size is selected to provide reasonable precision around key feasibility metrics (treatment initiation, tier attainment, and adherence), and to generate preliminary estimates of variability in symptom change to inform a future randomized trial. With *n* = 20 participants who initiate tDCS, an observed feasibility proportion in the range expected for home-based neuromodulation (e.g., 60%–80%) would yield a 95% confidence interval width of ~0.34–0.40 (approximately ±0.17–0.20), which is adequate for feasibility decision-making and for informing go/no-go thresholds for subsequent trials. To account for anticipated attrition and scheduling-related drop-off before surgery, we will enroll *n* = 24–25 participants, targeting *n* = 20 evaluable participants who initiate treatment and contribute preoperative outcome assessments.

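### The primary feasibility proportions use conflicting denominators (enrolled or initiated), and 'initiate' has two meanings, so enrolled people who never start fall out of the go criterion

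*Protocol article*

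**What the plan says.** All places are in the protocol article.

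- **Primary outcomes: feasibility and acceptability.** Initiation is "the proportion of enrolled participants who complete at least 15 tDCS sessions within the first 21 days". Exposure is "the proportion of participants achieving each pre-specified exposure tier prior to surgery", with no statement of which participants.
- **Feasibility criteria.** Criterion 1 requires that "≥ 60% of initiated participants achieve the minimum preoperative exposure target (Tier A, ≥15 total sessions completed before surgery". The section names recruitment as a domain but gives no recruitment or start-rate threshold among its four criteria.
- **Analysis populations.** "The primary analytic population will include all enrolled participants who initiate the tDCS intervention".
- **Figure 3 legend.** "All participants are included in the primary as-treated analysis by exposure tier achieved".
- **Primary analyses.** The initiation and tier proportions are again given over participants, without qualification.
- **Objectives and hypotheses.** The hypothesis is that most enrolled participants will "initiate treatment, defined as completion of the tDCS initiation phase within the first 3 weeks".
- **Dosing schedule.** The initiation phase is five sessions a week for three weeks, 15 in total.
- **Sample size justification.** The precision statement takes n = 20 as those who initiate. The enrolment target of 24 to 25 is then set to yield 20 "evaluable participants who initiate treatment and contribute preoperative outcome assessments".

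**The concern.** The primary objective asks whether surgical candidates can initiate and sustain the regimen despite variable surgical timing and competing demands. A person who enrols and never starts, for example because surgery is brought forward, is a failure on that question. The outcome definition counts that person. The primary population and criterion 1 do not.

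Two things are at stake. First, a primary outcome defined over enrolled participants cannot be computed in a population that leaves out non-starters, so the analyst must overrule one section or the other. Second, the go decision depends on a word the document uses in two senses. In one sense (first use) criterion 1 ignores failure to start; in the other (phase completed) it cannot fail.

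**Working it through.** **1. The plan's own figures.** The stated 95% interval width is about 0.34 to 0.40 for n = 20 at 60% to 80%. The Wilson width is 2·z·√[p(1−p)/n + z²/(4n²)] / (1 + z²/n), with z = 1.96.
- n = 20, p = 0.60: 0.395 (interval 0.387 to 0.781).
- n = 20, p = 0.80: 0.335 (interval 0.584 to 0.919).

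These match to rounding. The enrolment target also reproduces: 20/(1 − 1/6) = 24 and 20/(1 − 0.20) = 25, an allowance of 16.7% to 20%.

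**2. The sections side by side.**

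| Section | Quantity | Denominator | Pass mark |
|---|---|---|---|
| Primary outcomes | ≥15 sessions within 21 days | enrolled | none |
| Primary outcomes | each tier before surgery | participants | none |
| Feasibility criteria | ≥15 sessions before surgery | initiated | 60% |
| Analysis populations | primary population | enrolled who initiate | – |
| Figure 3 legend | primary as-treated analysis | all participants | – |
| Primary analyses | both proportions | participants | none |

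Two denominators are explicit, enrolled and initiated. The unqualified entries do not settle which applies.

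**3. Two meanings of initiate.**
- *First use.* The denominator is starters, and never-starters are left out of criterion 1.
- *Phase completed (Objectives and hypotheses).* Everyone in the denominator has at least 15 sessions within three weeks. Tier A is at least 15 sessions before surgery. Numerator and denominator coincide, for example 12/12 = 100%.

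**4. Size under the first-use meaning.** The document gives no start rate, so the number of starters is assumed. The 60% mark needs 12 of 20, 14 of 22, 15 of 24 or 15 of 25.

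| Reaching Tier A | of 20 starters | of 24 enrolled | of 25 enrolled |
|---|---|---|---|
| 12 | 60% | 50% | 48% |
| 13 | 65% | 54% | 52% |
| 14 | 70% | 58% | 56% |
| 15 | 75% | 63% | 60% |

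With 20 starters, counts of 12, 13 and 14 fall on opposite sides of 60%. With 22 starters among 25 enrolled, only 14 does (14/22 = 64%, 14/25 = 56%).

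The chance of such a split with 20 starters and 25 enrolled is P(X ≥ 12) − P(X ≥ 15), with X binomial on 20:
- true rate among starters 60%: 0.596 − 0.126 = 0.47
- 70%: 0.887 − 0.416 = 0.47
- 80%: 0.990 − 0.804 = 0.19

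**5. Precision on all enrolled (Wilson).**
- n = 24: width 0.365 at 60% and 0.308 at 80%.
- n = 25: width 0.359 at 60% and 0.303 at 80%.

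That is about 0.30 to 0.37, slightly narrower than the stated range.

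**The case against.** The best defence is that initiation and exposure are presented as two complementary domains. One proportion over enrolled and another over starters is a coherent design, and the numerators differ (within 21 days, or any time before surgery). Never-starters are counted as failures in the initiation outcome as defined. Starters who later drop out stay in, because Exposure tiers analyses people whether or not they proceed to surgery. Criterion 2 sets a separate retention mark of at least 50% at the preoperative assessment, and a CONSORT-style flow would normally show non-starters.

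Much of this stands, and it rules out three stronger readings.

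- A reader might infer a third denominator from the evaluable participants under Sample size justification. That phrase states a recruitment target; no proportion is defined over it.
- A reader might infer that the same data give both go and no-go. The 60% mark appears once, with one named denominator, and the enrolled-based outcome has no pass mark. For a fixed meaning of initiated, criterion 1 gives one answer. The split probabilities show how far the choice of denominator matters, not that the rule contradicts itself.
- A reader might infer that every proportion is biased upward. The initiation outcome as defined is not.

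The defence does not reconcile the enrolled-based primary outcome with a primary population of initiators, or with a legend that includes all participants. The retention mark does not state its denominator and is not a start-rate criterion. Nor does the defence address the two meanings of initiate.

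**Conclusion.** The concern holds in a limited form. The denominators of the primary feasibility proportions conflict, enrolled people who never start are left out of criterion 1, and nothing in the feasibility criteria catches them. Under the definition in Objectives and hypotheses, criterion 1 would be met automatically. That is probably not intended, since elsewhere initiating reads as first use, but the document does not exclude it.

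With 20 starters among 25 enrolled, the enrolled-based rate is 12 to 14 percentage points below the starter-based rate for 12 to 14 attainers. The gap shrinks as more people start and disappears if all do. These start numbers are assumptions. The correction should be made because it affects the go decision and is cheap before enrolment.

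**What to change.** 1. Define initiated once, as at least one session started, and reword Objectives and hypotheses so that finishing the initiation phase has a different name.
2. Use all enrolled participants as the denominator for the initiation outcome, tier attainment and criterion 1, counting never-starters as not attained.
3. Report started/enrolled as its own line, and the starter-based rate as secondary.
4. Align the Figure 3 legend, Analysis populations and Primary analyses with this.
5. In Sample size justification, limit the evaluable set to the MADRS-S change and restate precision for 24 to 25 enrolled (Wilson width about 0.30 to 0.37 at 60% to 80%).

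The cost is wording; no extra data are needed. The reported proportion may be lower and the 60% mark harder to meet: 15 of 24 or 25 enrolled, against 12 of 20 starters. If the sponsor regards 60% as suited only to starters, the mark for enrolled participants should be settled before enrolment begins.

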#### Exploratory clinical outcomes: depressive symptoms

Clinical outcomes are exploratory (Table 1). The principal exploratory clinical outcome is change in depressive symptom severity measured using MADRS-S. Depressive symptoms will be assessed at baseline (week 0) before initiation of tDCS, at week 1, at the end of the initiation phase (week 4), at week 7, and at a preoperative assessment conducted within a defined window before surgery (week 8–10+). Observed changes in depressive symptom severity will be interpreted in the context of the study’s feasibility-focused design. These analyses are not intended to establish efficacy, but rather to generate preliminary signal and variability estimates to inform future trial design.

**Table 1 tab1:** Exploratory outcomes.

Domain	Measure	Baseline	Timepoints*	Pre-op**	Post-op
Depression	MADRS-S	X	X	X	—
Spine disability	Oswestry disability index (ODI)	X	—	X	X (6 wks or 3 mos)
Pain intensity	Back pain NRS (0–10)	X	X	X	X
	Leg pain NRS (0–10)	X	X	X	X
Pain-related function	PROMIS pain interference (SF)	X	Optional	X	X
Physical function	PROMIS physical function (SF)	X	—	X	X
Opioid exposure	Baseline outpatient opioid use (MME)	X	—	—	—
Opioid utilization	Inpatient postoperative MME	—	—	—	X
	30-day outpatient postoperative MME	—	—	—	X

*Week(s) 0, 1, 4, 7, 10, and preoperatively (as applicable). **≤7 days before surgery.

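### Satisfaction, SUS and exit interview are stated only for the preoperative timepoint, with no collection at discontinuation, so the ≥4/5 acceptability mean may rest mainly on persisters and be too favourable

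*Protocol article*

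**What the plan says.** Acceptability is a primary outcome, shared with feasibility. Under *Primary outcomes: feasibility and acceptability* the Protocol article sets the timing of three instruments:

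- Satisfaction: "Treatment satisfaction will be assessed preoperatively using a structured questionnaire".
- Usability: the SUS yields a 0–100 "score, administered preoperatively".
- Interview: "A brief semi-structured exit interview will be conducted at the preoperative timepoint to capture qualitative themes".

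Under *Safety monitoring and stopping considerations* a fourth instrument has similar timing: "tDCS-specific AEs will be assessed via the tDCS Adverse Events Questionnaire preoperatively".

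No section shown describes giving any of these when treatment stops. For people who do not have an operation, *Follow-up schedule and study procedures* says: "Participants who do not proceed to surgery will continue to be followed for preoperative and intervention-related outcomes", "including depressive symptom trajectories, feasibility, and acceptability measures". It names no time at which the acceptability measures are then taken.

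*Feasibility criteria* makes acceptability a two-part test: a mean satisfaction/usability score of at least 4 out of 5, and no more than 20% discontinuation for device-related adverse effects or burden. A separate criterion accepts retention of 50% at the preoperative assessment. *Analysis populations* defines the primary population as all enrolled participants who start tDCS.

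**The concern.** A score taken once, late in the preoperative period, is available only for people still answering at that point. Someone who stops in week 2 contributes a satisfaction score, a SUS and an interview only if still in the study weeks later, and then from recall. Someone with no operation has no surgery date from which a preoperative timepoint could be counted.

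People who found the headset burdensome are plausibly the least likely to be reached. If so, the observed mean overstates acceptability among all who started, and the interview themes lean towards those who coped. The ≥4/5 limb is part of the test of whether the approach is feasible, so an optimistic mean could carry an unmodified procedure into the randomized trial. The mixed-model provision under *Missing data* does not help, because it concerns repeated measures and these instruments are stated for a single time.

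**Working it through.** **The plan's own figures.** The plan states no expected response rate or score for acceptability. Two related figures can be checked.

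- *Sample size justification* gives a 95% interval width of about 0.34–0.40 for proportions of 60–80% with n = 20. The Wilson interval gives 0.335 at 80% and 0.395 at 60%, so this reproduces. It concerns proportions and does not bear on the mean score.
- Enrolling 24–25 to obtain 20 evaluable implies a planned loss of 1 − 20/24 = 16.7% to 1 − 20/25 = 20%.

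**Inputs from the documents.** n = 20 initiators; pass mark 4 out of 5; discontinuation limit 20%; retention floor 50%.

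**Assumptions.** The scores of responders and non-responders are assumed, since the documents give none. The score is taken to run from 1 to 5. The 20% limit is taken as a share of initiators.

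**Formula.** With k responders among N initiators, responder mean c and non-responder mean m:

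all-initiator mean = (k·c + (N − k)·m) / N

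**Step 1: a case in which both limbs pass.** The 20% limit allows 0.20 × 20 = 4 device-related stops. Let those 4 be unmeasured at m = 2.8, and let 16 respond at c = 4.2.

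(16 × 4.2 + 4 × 2.8) / 20 = (67.2 + 11.2) / 20 = 3.92

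The observed mean is 4.2 (pass), discontinuation is 4/20 = 20% (pass) and retention is 16/20 = 80% (pass), but the all-initiator mean is below 4. The four would need to average (80 − 67.2) / 4 = 3.2 for it to reach 4.

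**Step 2: range over assumed non-responder scores, responder mean exactly 4.0.**

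| Responders | m = 1 | m = 2 | m = 3 | m = 4 |
|---|---|---|---|---|
| 10 of 20 (retention floor) | 2.5 | 3.0 | 3.5 | 4.0 |
| 16 of 20 (about the planned loss) | 3.4 | 3.6 | 3.8 | 4.0 |

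For example, (10 × 4.0 + 10 × 2) / 20 = 3.0.

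**Step 3: a higher responder mean.** With c = 4.5, non-responders must average (80 − 10 × 4.5) / 10 = 3.5 at 50% response, but only (80 − 16 × 4.5) / 4 = 2.0 at 80% response, for the all-initiator mean to reach 4. The conclusion is fragile when response is low or the observed mean is near 4, and fairly robust otherwise.

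**The case against.** The strongest reply is that the plan already reaches early stoppers by other routes, and much of it stands.

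- **Safety data.** A reader might infer that the adverse-effect profile, and so the safety criterion, also describes only persisters. The documents do not support that: "Safety monitoring will occur throughout the intervention via participant self-report, scheduled study team check-ins, and systematic documentation of adverse events". Intolerance at onboarding is documented, reasons for stopping are recorded and categorized, and adverse events are summarized overall and by phase. Serious events and psychiatric escalation do not depend on the questionnaire. For that questionnaire, 'preoperatively' may also mean the whole preoperative period.
- **Participants without surgery.** A reader might infer that they are left out. They are not: acceptability follow-up is promised for them, and only the time is missing.
- **The discontinuation limb.** A larger example is tempting: 12 responders at 4.2 and 8 burdened stoppers at 2.8 give (50.4 + 22.4) / 20 = 3.64. But 8/20 = 40% stopping for burden fails the 20% limb, so the acceptability criterion would fail anyway. The limb catches part of the problem, though not stops up to its limit or stops given another reason. The latter carry no presumption of dissatisfaction.
- **The window.** The "≤7 days before surgery" footnote belongs to the table of exploratory outcomes, which does not list these instruments. It should not be read as their stated window.
- **Staying in the study.** Stopping stimulation is not withdrawal, and assessments may be remote, so some who stop will still answer. The 50% figure is a pass mark, and the planned loss is about 17–20%.
- **Supplementary Table S1.** It is not shown and may add timepoints.

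What remains is that a recorded reason for stopping is not a satisfaction score, a SUS or an interview, and the text provides no trigger for these three when treatment ends early.

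**Conclusion.** The point holds for the satisfaction items, the SUS and the exit interview. As described, they are collected at one preoperative timepoint, with none at discontinuation and no defined time for participants without surgery. The ≥4/5 mean may therefore be inflated relative to the all-initiator population. That it is inflated cannot be shown, because response and non-responder scores are unknown.

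The size is modest if losses stay near plan and larger at the retention floor. With 16 of 20 responding at an assumed 4.2 and 4 unmeasured at an assumed 2.8, the mean falls by 0.28 to 3.92, a small shift that crosses the threshold. With a responder mean of 4.0 and half missing, it lies between 2.5 and 4.0 for non-responder means of 1 to 4. These figures assume a 1–5 score and that Supplementary Table S1 adds no end-of-treatment collection. The finding does not extend to the safety criterion.

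**What to change.** 1. Collect the satisfaction items, SUS and exit interview at end of treatment for every initiator: within about 7 days of the last session or of discontinuation for any reason, or at week 10 if there is no surgery. Use the remote assessment and electronic capture already planned.
2. Give the tDCS Adverse Events Questionnaire at the same trigger, and state whether 'preoperatively' means one assessment or the whole preoperative period.
3. Define the denominator of the ≥4/5 criterion as all initiators.
4. Report the response rate beside the mean, with a sensitivity range of assumed scores for non-responders, as in Step 2 above.
5. If Supplementary Table S1 already contains such a trigger, bring the text into line with it.

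The cost is slightly more participant time and a few remote interviews at discontinuation. No new instrument is needed. The change should be made before enrollment, since views at the time of stopping cannot be recovered later.
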